Studies have suggested that PSF involves neural networks beyond M1 [20–22]. A pharmacological trial showed that functional connectivity of the fronto-striato-thalamic network predicted Modafinil induced PSF reduction [34]. Fronto-striato-thalamic network has been implicated in other pathological fatigue [35–37] and is likely to play a role in PSF [38]. Further, because the fronto-striato-thalamic network is anatomically and functionally connected to M1, altered M1 excitability after stroke is likely related to connectivity in this network [39,40]. Therefore, tDCS applied to M1, in addition to changing M1 excitability, might also modulate the fronto-striato-thalamic network and result in reduced PSF. Examining both brain excitability and connectivity might shed light on the underlying mechanism of PSF and the working mechanism of tDCS on PSF.

The purpose of this double-blind, randomized controlled trial is to investigate the effects of multiple sessions of anodal tDCS to ipsilesional M1 on PSF and underlying neurophysiology. We hypothesize that compared to the sham group, the anodal tDCS group will show a greater decrease in fatigue and the effect will last up to 1 month (Aim 1). We also hypothesize that compared to sham tDCS, anodal tDCS will significantly increase ipsilesional M1 excitability and the functional connectivity between ipsilesional M1 and the fronto-striato-thalamic network (Aim 2). Lastly, we hypothesize that individuals who show a greater change in the neurophysiological outcomes (M1 excitability, brain connectivity) will demonstrate a greater reduction in fatigue (Aim 3).

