#### Clinical and behavioral assessments and outcomes.

The primary outcome for fatigue will be the Fatigue Severity Scale (FSS) score. FSS is a self-report questionnaire measuring the severity and impact of fatigue [41]. The FSS contains nine items rated on a 7-point Likert scale (1 = strongly disagree and 7 = strongly agree). The total score ranges from 9 to 63 with a higher score indicating greater fatigue. The FSS has been validated in chronic stroke [49]. Secondary measures of fatigue will be the Fatigue Scale of Motor and Cognitive Functions (FSMC) and Visual Analog Scale-Fatigue (VAS-F). The FSMC is a self-report questionnaire developed to measure cognitive and motor fatigue separately [50] and has been validated in chronic stroke [51]. The FSMC contains 20 items (10 for cognitive fatigue and 10 for motor fatigue) rated on a 5-point Likert scale. The total score ranges from 20 to 100 with a higher score indicating greater fatigue. The Visual Analog Scale-Fatigue (VAS-F) is a numerical scale ranging from 1-10 with a higher value indicating a higher level of global fatigue [52].

We previously showed that individuals with PSF reported high perceived effort during reaching and exhibited poor reach performance [16]. In the current study, we will adopt the same reaching task to evaluate changes in perceived effort and reach performance as a secondary measure of fatigue. At each assessment time point, participants will perform goal-directed reaches as fast and accurately as possible toward four targets that vary in distance and direction on a digitized tablet in sitting. Participants will also reach toward two central targets at both self-selected and fast speeds (i.e., as fast as possible) to evaluate the discrepancy between their movement choice (self-selected) and their capability (fast) [16]. Borg Rating of Perceived Exertion (Borg RPE) [53] and Paas Mental Effort Rating Scale (Paas MERS) [50] will be used to quantify perceived physical and mental effort associated with reaching, respectively. Borg RPE ranges from 6–20, with a higher value indicating greater perceived physical exertion. Paas MERS is a 9-point Likert scale that ranges from 1 (very, very low mental effort) to 9 (very, very high mental effort).

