#### Neurophysiological assessments and outcomes.

A TMS device (The Magstim Company Ltd, Whitland, UK) will be used to quantify changes in cortical excitability. Surface electromyography electrodes will be placed on the affected FDI and triceps muscles while participants are seated. Each participant’s structural brain MRI will be used to guide TMS coil placement using the Brainsight Neuronagivation system (Rogue Research, Canada). For each muscle, the following TMS outcomes will be derived: resting motor threshold (RMT), motor evoke potential (MEP) amplitude, input-output curve, short-interval intracortical inhibition (SICI), and intracortical facilitation (ICF).

RMT is the minimum stimulus intensity to elicit an MEP ≥ 50 µV in amplitude in at least 3 of 5 consecutive stimulations. MEP will be elicited at rest with a stimulus intensity at 120% of RMT and at 100% maximal stimulation output. The averaged peak-to-peak MEP amplitude will be calculated to index corticospinal excitability. We will also construct an input-output curve using six stimulation intensities (100–150% of RMT) to assess corticospinal excitability and motor recruitment. Both intracortical inhibition (SICI) and facilitation (ICF) of M1 will be measured with the conditioning stimulus set at 80% RMT and the test stimulus intensity set at 120% RMT. SICI will be elicited at an inter-stimulus interval of 2 ms whereas ICF will be elicited at an inter-stimulus-interval of 15 ms. The primary measure of brain neurophysiology will be the input-output curve slope obtained from the FDI with a steeper slope indicating greater excitability [54]; all other TMS measures will serve as exploratory outcomes.

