To examine effects on clinical, behavioral, and neurophysiological outcomes, we will perform a 2 group (anodal, sham) x 3 time point (baseline, post-intervention, follow-up) repeated measure ANOVA/ANCOVA. Resting state functional MRI data will be analyzed with a 2 group x 2 time point (baseline, post-intervention) ANOVA/ANCOVA. Post-hoc Bonferroni-adjusted comparisons will be completed if a main effect or interaction is detected. To examine whether individuals who show a greater change in neurophysiological outcomes demonstrate a greater reduction in PSF, Pearson or Spearman correlational analyses will be run to examine the relationship between changes in neurophysiological measures (input-output curve, fronto-striato-thalamic network connectivity) and changes in PSF (FSS). The strength of relationships will be interpreted as follows: r < 0.25 = little or no relationship; r of 0.25 to 0.5 = fair; r of 0.5 to 0.75 = moderate; and r > 0.7 = strong relationship [58].

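### Aim 3 correlates change scores with no term for arm, so a tDCS effect on both measures could by itself produce a correlation; separately, the printed strength bands overlap

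*Protocol article*

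**What the plan says.** In the Protocol article, the Introduction sets out the third hypothesis: "individuals who show a greater change in the neurophysiological outcomes (M1 excitability, brain connectivity) will demonstrate a greater reduction in fatigue (Aim 3"). The analysis is in Data management and data analysis: "Pearson or Spearman correlational analyses will be run to examine the relationship between changes in neurophysiological measures" (input-output curve and network connectivity) and changes in FSS. That paragraph gives the ANOVA models a group factor, but mentions arm nowhere in the correlation analysis. It does not say whether the arms are pooled, analysed separately or adjusted for.

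Strength is then graded on a scale attributed to a cited source: "r < 0.25 = little or no relationship; r of 0.25 to 0.5 = fair", followed by "r of 0.5 to 0.75 = moderate; and r > 0.7 = strong relationship". No absolute-value sign is shown, and the coding of FSS change is not given.

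The first two hypotheses in the Introduction matter here. For fatigue, "the anodal tDCS group will show a greater decrease in fatigue and the effect will last up to 1 month (Aim 1"). For the brain measures, "anodal tDCS will significantly increase ipsilesional M1 excitability and the functional connectivity" with the fronto-striato-thalamic network.

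**The concern.** Aim 3 asks whether the people whose brain measures change more are the people whose fatigue falls more. A bivariate correlation over the whole randomised sample does not isolate that question. If anodal tDCS raises the brain measure and lowers FSS, the anodal participants sit in one corner of the scatter plot and the sham participants in the other. A correlation follows from the separation of the two clusters alone. It would restate Aims 1 and 2 rather than add evidence on mechanism, and the distortion is largest when those two aims succeed. The Discussion relies on these data for the working mechanism of tDCS in post-stroke fatigue, so the distinction matters for what the trial can claim.

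The strength scale has a separate, smaller fault: two of its bands claim the same values of r.

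**Working it through.** **The plan's own figure.** The article gives no sample size or power for Aim 3. Its sample size for the repeated measures ANOVA reproduces. With f = 0.25, correlation 0.5, two groups and three time points, λ = f²·N·m/(1 − ρ) = 0.0625 × 28 × 3/0.5 = 10.5 on 2 and 52 df. Power is 0.812, and 28 is the smallest even N that reaches 0.80. Then 28/0.9 = 31.1, which gives 32 with equal arms. N = 28 and N = 32 are used below.

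**Expected correlation when the arms are pooled.** Scale each change score to a within-arm SD of 1. Let the anodal arm shift by +d on the brain measure and by −d on FSS, with 1:1 allocation and zero correlation within each arm. Each pooled variance is 1 + d²/4 and the pooled covariance is −d²/4, so

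|r| = (d²/4)/(1 + d²/4).

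- d = 0.5: 0.0625/1.0625 = 0.06
- d = 0.8: 0.16/1.16 = 0.14
- d = 1.06: 0.281/1.281 = 0.22
- d = 1.5: 0.5625/1.5625 = 0.36

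With unequal shifts the numerator is dₓd_y/4, so the artefact vanishes if tDCS moves only one of the two measures.

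**Where d = 1.06 comes from.** Suppose the arms differ by δ at post-intervention, either sustained to follow-up (0, δ, δ) or not (0, δ, 0). In both patterns the interaction variance over the six cells is δ²/18, so δ = f·√18 in units of the outcome SD. With ρ = 0.5, the SD of change is √(2 × (1 − 0.5)) = 1 in the same units. Hence d = 0.25 × 4.243 = 1.06. At f = 0.35, which the article says earlier fatigue studies exceeded, d = 1.48.

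**Rejection rate.** This was simulated with normal data and Pearson correlation at two-sided 5%, using 40,000 runs per cell (100,000 for d = 1.06 and 1.48).

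| d | Unadjusted, N = 28 | Unadjusted, N = 32 | Arm partialled out |
|---|---|---|---|
| 0.5 | 5.8% | 6.0% | 4.8–4.9% |
| 0.8 | 10.8% | 11.5% | 4.8–4.9% |
| 1.06 | 20.9% | 23.3% | 4.9–5.1% |
| 1.48 | 49.9% | 55.8% | 5.0–5.1% |
| 1.5 | 50.9% | 57.0% | 4.9–5.0% |

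At d = 1.06, |r| is 0.25 or more in 45–47% of trials. Chance alone gives about 17–20% at these sample sizes.

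**The bands, read as printed.**

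- r = 0.5: fair and moderate
- r = 0.72: moderate and strong
- r = 0.75: moderate and strong
- r = −0.3, −0.6 and −0.8: all in the lowest band

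On direction, the FSS section says "The total score ranges from 9 to 63 with a higher score indicating greater fatigue", and the input-output curve is read "with a steeper slope indicating greater excitability". If FSS change is later minus baseline, the hypothesis predicts a negative r. If change is coded as reduction, it predicts a positive r.

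**The case against.** The strongest objection is that pooling is not in the text. The article does not say the arms are combined, and a condensed article may leave the handling of arm to a fuller document. That stands as a limit: pooling is an inference. It is the natural one, because the hypothesis speaks of individuals without restriction, the named method has no group term, and the covariate rule in the same section concerns baseline differences in the primary analyses. The point is therefore about a named method that does not isolate its question, not about missing detail.

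A reader might also infer that the scale would dismiss every hypothesised result as no relationship. The documents do not support that. The hypothesis is worded as a reduction in fatigue, which could be coded positive; such bands are ordinarily applied to |r|; and the p-value does not depend on the label. The sign needs a clarifying clause and nothing more.

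The size is also open to challenge. The article cites effect sizes for fatigue only, so applying the same d to slope or connectivity is an assumption. At d = 0.5 the inflation is almost nil. Calling the rejections false positives treats zero within-arm correlation as the null, which the hypothesis does not state in those terms. All of this stands, and it is why a range is shown.

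**Conclusion.** The arm adjustment is a cheap improvement; the overlapping bands are a rule that is wrong as written.

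If Aim 3 is analysed over all participants without arm, the chance of a significant correlation with no within-arm relation runs from about 6% to 51–57% over d = 0.5 to 1.5, and is 21–23% at the planning effect size. This rests on whole-sample analysis, equal shifts on both measures, normal data and Pearson correlation. Spearman was not simulated, but a shift between arms moves ranks in the same way. The documents do not establish that the arms will be pooled, so this is a risk on the natural reading and not a demonstrated error.

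The overlap needs no assumption: the two printed limits, 0.75 and 0.7, cannot both stand. Its effect is confined to the descriptive label and changes no estimate or test.

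**What to change.** 1. Specify Aim 3 as a partial correlation (Pearson or rank-based), or a regression of FSS change on neurophysiological change, with arm as covariate. In the simulations this returns the rejection rate to about 5%. It needs no new data and costs one degree of freedom.
2. Choose one upper cut-point, 0.70 or 0.75, after checking the cited source; the article cannot settle which was meant. Make the bands contiguous, and assign 0.5 to one band only.
3. Apply the bands to |r|, and state how FSS change is coded and which sign is expected.

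Baseline covariates and a separate anodal-arm estimate are optional. Neither is needed to remove the artefact. The anodal-arm estimate would be imprecise: r = 0.40 at n = 16 has a 95% confidence interval of about −0.12 to 0.75.

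The article expects data collection to end in July 2026, so the wording can be settled before then.

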### Ethics and monitoring

Ethical approval has been obtained from the Texas Woman’s University Institutional Review Board (FY2023−226). The PI will obtain the informed consent and all participants will provide written informed consent. An independent Data Monitor and Safety (DMS) officer will review study progress, protocol deviations, and adverse events on a quarterly basis. Adverse events will be documented and reviewed by the investigators quarterly. Serious adverse events will be reviewed immediately and reported to the IRB and DMS officer. Protocol amendments will be reported to the DMS officer, IRB and funding agency. Interim analysis is not planned for this trial. In the events of serious adverse events, participant’s group assignment will be unblinded.

## Discussion

This study will address a long-standing problem in stroke recovery, PSF, with a novel and evidence-based intervention, tDCS, and a robust double-blind randomized controlled design. Our rich dataset composed of clinical, behavioral, neurophysiological and neuroimaging data will assist in a thorough evaluation of the effects of tDCS on PSF.

PSF is a complex, multifactorial phenomenon and likely require a multimodal approach for effective management. We propose to use neuromodulation based on the association between PSF and altered brain excitability and connectivity. Modulating brain excitability via non-invasive brain stimulation not only offers an alternative to pharmacological approaches but also provides a more targeted intervention. Previously examined strategies that have been found to be effective in reducing PSF include graded physical activity [59], cognitive-behavioral training [60], and central acting pharmacological agents [61]. These strategies share a common feature, inducing neuroplasticity. Compared to non-invasive brain stimulation, these strategies are less targeted which may contribute to variability in responses. Non-invasive brain stimulation, such as tDCS, is effective in promoting motor recovery after stroke [32] and holds promise as a treatment of non-motor symptoms such as PSF. In the current study, we choose tDCS as the non-invasive brain stimulation tool because it is safe, tolerable, and produces minor transient side effects compared to other non-invasive brain stimulation techniques such as repetitive TMS, making it a promising tool to be integrated into clinical practice.

In addition to clinical evidence, our study will generate rich neurophysiological data to advance our understanding of the neural mechanism of PSF and the working mechanism of tDCS on PSF. Our unique approach of using both TMS and functional MRI will provide a comprehensive investigation of the underlying neural mechanisms. We will use TMS to assess M1 excitability and expect that changes in M1 excitability will be associated with changes in clinical outcomes. However, tDCS applied to M1 will also alter activity in remote areas [39,40], including networks that might play a role in PSF. We therefore include functional connectivity as our secondary outcome to complement the TMS measures. Using both TMS and functional MRI will provide crucial information of the underlying mechanisms of PSF, which may assist in formulating more targeted interventions in the future. Further, our design includes both clinical self-reported measures (e.g. FSS) and behavioral outcomes (e.g. perceived effort during reaching) of PSF. These clinical and behavioral outcomes will permit us to link the neurophysiological effects to behavioral manifestations.

The current study has a few limitations. We will implement tDCS as a stand-alone treatment. Previous studies in motor rehabilitation have shown that the effect of non-invasive brain stimulation is optimized when it is combined with other interventions [62,63]. The current study will establish the efficacy of tDCS on PSF in preparation for future studies that combine tDCS with other PSF management strategies. Parameters for tDCS such as the electrode sizes were selected based on safety guidelines and previous pathological fatigue investigations [25,27,64]. These parameters might not be most effective in reducing PSF. However, optimizing tDCS parameters, in our view, should be the next step once the working mechanism of tDCS in reducing PSF is better understood. Because there is no evidence to support the connection between stroke lesion characteristics and PSF [22], we will not control for lesion. However, responsiveness to tDCS might be determined by stroke lesion characteristics [65]. Thus, it is possible that some participants will not show a response to tDCS. Our protocol involves structural and functional brain MRI and TMS assessments. These data will allow us to explore factors associated with tDCS responsiveness and provide information to guide future research. Lastly, functional MRI will not be conducted at follow-up due to insufficient resources. Therefore, the long-term effect of tDCS on the brain functional connectivity will not be examined in the current trial.

## Conclusion

This double-blind randomized controlled trial will determine the behavioral and neurophysiological effects of 5 daily sessions of tDCS on PSF. Trial results will inform the clinical treatment of PSF as well as provide important information on the mechanisms of PSF and its responsiveness to tDCS.

### Clinical trial registration

This protocol is registered on Clinicaltrials.gov (NCT06088914).
